#### Cognitive Function Instrument

Cognitive Function Instrument (CFI) is a screening tool to detect early changes of ADL due to cognitive decline.^12^ It was developed by the Alzheimer’s disease Cooperative Study over the last decade. The questionnaire used can be found in online supplemental file 2. CFI consists of 14 questions that are related to functional ability changes as a result of cognitive impairments. It is brief and easily administered at home through post, telephone or transmitted electronically. The CFI score is calculated by summing 1 point for ‘Yes’, 0 point for ‘No’ and 0.5 for ‘Maybe’. Although the CFI questionnaire includes ‘self’ and ‘partner’ versions, this project uses the ‘self’ version, because the current surveillance set up did not allow for both versions.

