### Outline of studies included in the project

The four studies are briefly explained below and summarised in table 1.

**Table 1 T1:** Summary of studies

	Study 1	Study 2	Study 3	Study 4
Target population for recruitment	General Population (80 000)	Citizens with Possible Cognitive Decline (4131)	‘Frail Check’ Participants (4800)	Brain health school programme participants (80)
Sample population	50 155	2385	2705	57
Baseline evaluation	KCL	CFI, EQ-5D, GDS	CFI, EQ-5D, General Frailty Measures	MMSE, EQ-5D CFI, GDS, etc
Primary outcome	LTC Need	LTC Need	LTC Need	MMSE
Secondary outcome	LTC Need Level	CFI, EQ-5D	LTC Need Level	EQ-5D, CFI, Five Cog, etc
Intervention	None	None	None	Intensive Cognitive Training
Study period	4–5 years	2 years	2 years	30 months

CFI, Cognitive Function Instrument; GDS, Geriatric Depression Scale; KCL, Kihon Check List; LTC, long-term care; MMSE, Mini Mental State Examination.

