#### Study 2: quantifying the risk of LTC need in citizens with possible cognitive decline

This is a prospective cohort study which examines the predictive ability of CFI and EQ-5D questionnaires, for LTC certification, in elderly citizens at higher risk of dementia. The sample population is a subgroup population of those that responded to the KCL of 2015 (a subgroup of study 1). The target population are those that responded with unfavourable answers to either of the three cognitive domain questions in the KCL from the 2015 survey. The major inclusion criteria are citizens who are above or equal to 70 years old at the time of KCL survey, had at least one unfavourable answer to the cognitive domain questions in the KCL, those that responded to CFI and EQ-5D questionnaires in 2017 and 2019, and are not LTC certified. The target population is 4131 citizens which were sent CFI, and EQ-5D in 2017. Out of which 2981 citizens responded. In 2019, this same cohort were sent the CFI and EQ-5D, out of which 2444 citizens replied. After discounting for uncompleted forms, 2292 formed the sample for this study. The primary endpoint is the occurrence of LTC need certification after 2 years, and the secondary endpoints are the change in CFI and EQ-5D during the same period. After matching for LTC certification, statistical analysis will be carried out with the use of proportional Hazard model. Relative risk for future LTC need and death is estimated in relation to the baseline CFI and EQ-5D. The relationship between the changes in such parameters and LTC need will also explored. Repeated measure analysis of variance (ANOVA) or mixed effect model will be used to examine the changes of CFI and EQ-5D, in relation to occurrence of LTC need.

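### Study 2 removes 152 of 2444 repliers for uncompleted forms, including from its primary LTC endpoint, although completeness is not a listed criterion and the outcome comes from municipal records

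*Protocol article*

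**What the plan says.** The Study 2 section of the protocol article gives the participant flow in four steps.

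- Sent: "The target population is 4131 citizens which were sent CFI, and EQ-5D in 2017".
- Baseline response: "Out of which 2981 citizens responded".
- Second wave and sample, after both questionnaires went to the same cohort again in 2019: "out of which 2444 citizens replied. After discounting for uncompleted forms, 2292 formed the sample for this study".

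The response and certification parts of the listed criteria cover "those that responded to CFI and EQ-5D questionnaires in 2017 and 2019, and are not LTC certified". They require a response and do not mention completeness. The list is introduced as the major criteria only.

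The primary endpoint is LTC certification after 2 years. The secondary endpoints are the changes in CFI and EQ-5D over the same period. No separate sample is named for the primary endpoint, so the 2292 serve both. The proportional hazards analysis relates the outcome to baseline CFI and EQ-5D.

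Table 1 (Outline of studies included in the project) gives a different Study 2 sample, as the second figure in the row "Sample population 50 155 2385 2705 57".

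The LTC certification section explains that certification is done by the municipal office when a citizen applies. The Cognitive Function Instrument section defines the score as a sum over items: "The CFI score is calculated by summing 1 point for ‘Yes’, 0 point for ‘No’ and 0.5 for ‘Maybe". A blank item therefore has no value under the definition given.

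**The concern.** The criteria ask for a response, while the flow asks for a completed form. The stricter condition is applied to the whole study, including an endpoint that needs no second-wave form.

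What is at stake depends on the wave.

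- **Incomplete 2019 form.** The person may have a complete baseline and a known LTC outcome, which is all the primary analysis needs. Removing them conditions the sample on something observed at the end of the 2-year window. By then decline or certification may already have occurred and may have affected how the form was filled in. That is potential selection on the outcome.
- **Incomplete 2017 form.** A predictor value is partly missing. The cohort is aged 70 or over and was chosen for an unfavourable cognitive answer on the Kihon Check List (KCL), so blanks may be related to the trait the CFI measures. A postal screening programme would also receive such forms, and dropping them tests the instruments in a somewhat easier population.

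**Working it through.** **Inputs from the Study 2 section:** 4131 sent, 2981 responded in 2017, 2444 replied in 2019, 2292 in the sample. **From Table 1:** sample 2385. The 2292 is an observed count with no formula behind it, so the check is subtraction along the flow.

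**Step 1: size of the exclusion**
- On the text: 2444 − 2292 = 152, and 152/2444 = 6.2%.
- On Table 1: 2444 − 2385 = 59, and 59/2444 = 2.4%.
- The two sample figures differ by 2385 − 2292 = 93 (93/2385 = 3.9%), too much for rounding.

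**Step 2: place in the total loss**

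Assume the 2444 are all among the 2981 baseline responders, which the text does not state outright.
- Loss from requiring a 2019 reply: 2981 − 2444 = 537 (537/2981 = 18.0%).
- Total loss: 537 + 152 = 689 (689/2981 = 23.1%).
- Share of that loss due to uncompleted forms: 152/689 = 22%.

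The completeness rule is thus the smaller of two restrictions that can depend on second-wave data.

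**Step 3: possible effect on incidence**

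Let p be the share removed and RR the 2-year LTC risk of removed people relative to retained people. RR is an assumption; the article gives no data on it.
- Factor by which incidence among all repliers exceeds that among retained people: 1 + p(RR − 1).
- Share of LTC events lost: p·RR / [1 + p(RR − 1)].

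| RR (assumed) | Factor, p = 6.2% | Events lost, p = 6.2% | Factor, p = 2.4% |
|---|---|---|---|
| 1 | 1.00 | 6% | 1.00 |
| 1.5 | 1.03 | 9% | 1.01 |
| 2 | 1.06 | 12% | 1.02 |
| 3 | 1.12 | 17% | 1.05 |

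A second illustration uses the 3-year incidences that the Discussion reports from a prior study: 6.4%, 12.6% and 29.6% for one, two and three unfavourable KCL cognitive answers. Suppose the retained 2292 have 6.4%. If the 152 have 6.4%, 12.6% or 29.6%, then (2292 × 6.4% + 152 × r)/2444 gives 6.4%, 6.8% or 7.8% overall. The last case is extreme, since it gives everyone removed the risk of the worst KCL group.

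**Step 4: which data each endpoint needs**

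| Endpoint | 2017 form | 2019 form | LTC record |
|---|---|---|---|
| LTC certification (primary) | yes | no | yes |
| Change in CFI and EQ-5D (secondary) | yes | yes | only when related to LTC need |

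Only the change endpoints can justify requiring a complete 2019 form.

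**The case against.** Much of the case on the other side stands.

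- A reader might infer that the 152 meet every listed criterion. The article does not show this. Absence of LTC certification is also listed, matching to LTC records is mentioned only after the sample is formed, and the list covers major criteria only. Having responded could even be read as having answered both questionnaires in full.
- A reader might infer that one blank CFI item removes a person, or that the incomplete form is the cognitive one. Neither is stated. An uncompleted form could be a blank return, a missing instrument or an unscorable EQ-5D, in either wave.
- A reader might infer that the exclusion biases the main result. The planned analysis estimates relative risk by baseline CFI and EQ-5D. If incompleteness depends only on those predictors, a complete-case hazard ratio need not be biased. The factors in the table concern incidence and rest on assumed risk ratios.
- Detailed missing-data methods are commonly left to a fuller document, so their absence from an article is not a fault.

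These points limit the claim but do not remove it. The article states an actual exclusion and the sample that results, so this is not a detail left for later. The argument about the hazard ratio covers exclusion that depends on the baseline predictor. It does not cover exclusion based on a 2019 form, which can depend on the outcome. The LTC outcome does not require a completed form.

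**Conclusion.** The point holds in limited form. On the Study 2 text, 152 of 2444 repliers (6.2%) leave the sample for uncompleted forms, under a condition not among the listed criteria. On Table 1 the number would be 59 (2.4%). The two sample figures contradict each other and must be reconciled.

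The firm part concerns 2019 forms: an incomplete one is no reason to leave the primary analysis, and using it as one can select on the outcome. How many of the 152 this affects is not given; it could be none or all.

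The weaker part concerns 2017 forms. A link between incompleteness and decline is plausible in this cohort, but no passage gives data on it. If the removed people carry 1.5 to 3 times the risk of the others, incidence is understated by a factor of 1.03 to 1.12 on the text's figures, or 1.01 to 1.05 on Table 1's. The true direction and size are unknown, and the effect is probably modest. No bias in the hazard ratio has been shown.

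**What to change.** 1. State which form and which wave were incomplete, and what counted as uncompleted. Reconcile 2292 with 2385.
2. Define the primary-endpoint sample by a returned 2017 form and no LTC certification at that time. This also lifts the 2019-reply condition for the primary endpoint, so the sample could reach 2981, less those already certified. The 6.2% does not measure that wider change.
3. Impute missing baseline CFI and EQ-5D items from the answered items, age, sex, the 2015 KCL answers and the LTC outcome. The KCL answers should be available because Study 2 is a subgroup of Study 1.
4. Report LTC incidence for incomplete and complete forms side by side. This alone would show whether the exclusion matters.
5. Keep the complete-form analysis as a sensitivity analysis, and require a complete 2019 form only for the change endpoints.

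All of this uses data the project already holds or plans to link. The cost is some extra analysis and reliance on an imputation model for what is probably a small share of records; the number of incomplete 2017 forms is not given.

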#### Study 3: quantifying the risk of LTC need in generally healthier citizens

This study explores the relationship of CFI, EQ-5D and other frailty-related parameters, with the risk of future LTC need within 3 years. It will search for other prognostic factors that may predict the progression to LTC. The target population was Kobe residents who turned 65 years old in 2017 or 2018 and who underwent ‘Frail Kenshin’. ‘Frail Kenshin’ is an elderly citizen health check-up programme by Kobe city, which is offered to citizens covered by the ‘Kokumin Kenko Hoken’ insurance (Kokumin Kenko Hoken is the National Health Insurance system in Japan, it includes all Japanese citizens and long-term residents). ‘Kokumin Kenko Hoken’ insurance covered citizens who turned 65 in 2017 or 2018 were 28 800 citizens, out of which 2705 people appeared for the ‘Frail Kenshin’ check-up of 2017 and 2018 and formed the sample for this study. Thus, the target citizens are younger than study 1 and 2, and not known to be at risk for dementia. They are also likely to be health-conscious citizens since they appeared for a voluntary health check-up. The major inclusion criteria are those who turn or turned 65 years old during 2017 or 2018, underwent ‘Frail Kenshin’ check-up and were not LTC certified at the time of the check-up. The primary endpoint is the occurrence of LTC need, and the secondary endpoints include LTC care levels (1–5). CFI and EQ-5D questionnaires were carried out at the venue of check-up, concomitant with other frailty checks, and the completed questionnaires were collected and checked by the person in charge.

First the incidence of LTC over the study period will be calculated using LTC care level 1 or greater. The statistical methods to be used are logistic regression model (estimated by least absolute shrinkage and selection operator: LASSO) with the presence and absence of LTC care as the dependent variable with CFI Self score, EQ-5D scores and other ‘Frail Kenshin’ check-up results as explanatory variables. A formula and Receiver Operatorating Characteristic (ROC) curve will be estimated. Multiple regression will also be carried out for continuous variables used in the ‘Frail Kenshin’ health check-up. In addition, age and gender are included in the model as explanatory variables in all analysis. In the case that the significance level of the above-mentioned test is p<0.05 on both sides, the multiplicity of the tests is not considered an issue. SAS V.9.4 and R V.3.6 are used for the analysis.

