**Trial registration number:**

UMIN000023283.

Strengths and limitations of this studyThis research project includes population based studies that allow for simple and reliable assessments of the risk for future long-term care need.This research project uses big data, which are collected by the local government (municipal office).The various baseline measures give a broad instrument to use for the prediction of long-term care needs concomitant with cognitive decline.The duration of follow-up of respective studies, which range from 2–4 years, is limited and further longer-term studies will be required.Study 4 has limitations, since it is a small sample and limited single-centre intervention study.

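### Study 3's outcome horizon is 3 years in its aim but 2 years in Table 1, and its yes/no logistic outcome is tied to no fixed window from each check-up

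*Protocol article*

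**What the plan says.** All places are in the protocol article.

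- **Aim (Study 3 section).** CFI, EQ-5D and other frailty measures are related "with the risk of future LTC need within 3 years".
- **Table 1 (Outline of studies included in the project).** The row for Studies 1 to 4 reads "Study period 4–5 years 2 years 2 years 30 months". The third entry, 2 years, is Study 3's.
- **Primary endpoint (Study 3 section).** "The primary endpoint is the occurrence of LTC need, and the secondary endpoints include LTC care levels (1–5"). This sentence has no time point.
- **Entry (Study 3 section).** "2705 people appeared for the ‘Frail Kenshin’ check-up of 2017 and 2018 and formed the sample for this study".
- **Analysis (Study 3 section).** Incidence of LTC at care level 1 or above is calculated across the study period. A LASSO logistic model is then fitted "with the presence and absence of LTC care as the dependent variable", and a formula and ROC curve are derived from it. No follow-up time, per-person window or data cut-off is mentioned.
- **Strengths and limitations list.** "The duration of follow-up of respective studies, which range from 2–4 years, is limited". This covers the project as a whole and assigns no figure to Study 3.

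**The concern.** A logistic risk formula has meaning only for a stated length of time, and here two lengths are given. The analysis text takes its window from the study period, which is also the label of the Table 1 row. Read literally, the model would use 2 years while the aim promises 3, and a 3-year outcome cannot be fully observed in a 2-year follow-up.

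The horizon sets the absolute risk that the formula returns, the calibration target and the number of events available to the LASSO. Staggered entry adds a second, conditional problem. Unless everyone is assessed over the same length of time from their own check-up, a yes/no outcome treats different observation times as if they were equal.

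**Working it through.** **Step 1: compare the statements.** The article gives no sample size calculation, expected event count or LTC rate for Study 3, so there is no figure of the plan's own to reproduce. The horizon check is a direct reading: 3 years in the aim, 2 years in Table 1, none in the endpoint sentence. The Table 1 row matches follow-up length elsewhere: Study 2's 2 years agrees with its endpoint after 2 years, and Study 4's 30 months agrees with its monitoring period. It is therefore reasonable to read Study 3's entry as follow-up too.

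**Step 2: what the choice of horizon changes.** Inputs: N = 2705 (Study 3 section). The 3-year risk r3 is an assumption, varied from 0.5% to 3.5%. The top value equals the 3-year incidence that the Discussion reports for citizens with no unfavourable cognitive answers in an earlier Kobe analysis; it is not a rate for this cohort. With a constant hazard,

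h = −ln(1 − r3)/3, and r(2) = 1 − exp(−2h).

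For r3 = 1%: h = 0.01005/3 = 0.00335, and r(2) = 1 − exp(−0.0067) = 0.668%. Expected events are 2705 × 0.00668 ≈ 18 at 2 years and 2705 × 0.01 ≈ 27 at 3 years.

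| Assumed 3-year risk | 2-year risk | Events, 2 years | Events, 3 years | 2-year / 3-year risk |
|---|---|---|---|---|
| 0.5% | 0.334% | 9.0 | 13.5 | 0.667 |
| 1% | 0.668% | 18.1 | 27.1 | 0.668 |
| 2% | 1.338% | 36.2 | 54.1 | 0.669 |
| 3.5% | 2.347% | 63.5 | 94.7 | 0.671 |

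The shorter horizon has about one third less risk and one third fewer events, almost regardless of the assumed rate.

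**Step 3: what staggered entry would do, if outcomes were read at one calendar date.** Suppose, for illustration, that 2017 entrants had 3 years of observation and 2018 entrants 2 years. For small risks the ratio is 3/2 = 1.5; the exact odds ratio is 1.50 to 1.51 over the range above, with no true difference between the people. The pooled yes/no risk would be w·r(3) + (1 − w)·r(2), where w is the share entering in 2017. At r3 = 1% this is 75%, 83% or 92% of the 3-year risk for w = 25%, 50% or 75%. The 1.5 belongs to this 12-month contrast only. The widest gap between entrants cannot be sized without a cut-off date.

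**Step 4: one fixed window per person.** If each participant is assessed over the same completed window from check-up, the distortion in Step 3 is zero. The conflict in Steps 1 and 2 still has to be settled.

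**The case against.** The best defence is that the 3-year statement can be read as a fixed window from each person's check-up. A yes/no logistic model is then legitimate and entry year adds nothing. That stands: the choice of logistic regression is not in itself an error. It can also be said that the Table 1 row is used loosely, since Study 1 shows 4–5 years there and 4 years in its text. This weakens the table as a precise source, but nothing in the article resolves 2 against 3 years for Study 3.

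Three stronger readings are tempting and not supported.

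- **Follow-up is unequal as planned.** A reader might infer this from the staggered entry, perhaps by borrowing Study 1's cut-off of November 2019. With even entry from January 2017 to December 2018, that date would give about 11 to 35 months of follow-up, so nobody would reach 3 years. But the date is stated for Study 1 only, and the article gives no common calendar cut-off for Study 3. Nor does Study 1 offer a contrast in having a fixed personal window: it too stops at a calendar date, and differs in using time-to-event methods.
- **Deaths and departures from Kobe are counted as not needing care.** The article does not say how they are coded. That rule is commonly left to a fuller document, so its absence is no finding.
- **A Cox model is required.** With a fixed, completed window it is not.

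**Conclusion.** The contradiction is certain from the text: Study 3 has a 3-year aim, a 2-year study period and an analysis whose window is defined only by the study period. It affects the study's main product, the risk formula and ROC curve, and should be corrected. Its size is about one third of the absolute risk and of the event count, assuming a constant hazard; the event counts themselves rest on assumed rates, because none is given for this cohort.

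Unequal follow-up is a conditional risk and not a documented defect. It arises only if outcomes are read at one calendar date, and the 1.5-fold figure illustrates 3 against 2 years of observation at a constant low hazard.

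**What to change.** Choose one horizon that every participant can complete, count it from each person's own check-up date, and state it identically in the Study 3 aim, in Table 1 and in the Study 3 analysis text. Add it to the primary-endpoint sentence as well. In the logistic model, formula and ROC curve, count only LTC certifications that fall within that window.

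An acceptable alternative is a time-to-event model from the check-up date with a stated data cut-off. If it is used to report absolute risk, death should be treated as a competing event; simply censoring at death would overstate the risk of LTC certification.

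The first option is a wording change with the same data and software. Its only downside is fewer events if the shorter horizon is chosen, about one third fewer under the assumptions above.

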#### Study 4: study on effect of multimodal dementia prevention programme in community-dwelling elderly

This is a parallel exploratory intervention study, to explore the effects of multimodal interventions for slowing the process of cognitive decline. The target group were approximately 80 citizens over 70 years old who participated in a dementia prevention education programme which was held monthly by Kobe city in 2016. Individuals who agreed to participate in this study are randomly divided into two groups. Both groups undergo an intensive training programme (education, cognitive training and exercise) once a week for a total of 10 weeks and are monitored every 6 months for up to 30 months after recruitment. During the follow-up period, the intervention group receives a booster training once every 3 months, whereas the control group does not. The endpoints include changes in Mini Mental State Examination, CFI, EQ-5D, Five Cog, Timed Up & Go test, Physical Activity Scale for the Elderly and Geriatric Depression Scale. In the ANOVA between the three groups, effect size was set at 0.25, α=0.05 and power=0.80, the necessary data number will be approximately 50 persons for each group. Since this is a long-term longitudinal study, the number of subjects is set at a higher 100 persons, which is about double the necessary number (for statistical significance) as a cautionary measure for drop outs and missing data. The longitudinal change of the evaluation results in each group is analysed using repeated ANOVA and mixed effects model. The amount of change in the evaluation result between groups is compared by multiple comparison tests: the paired t-test or Wilcoxon test.

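### Study 4's sample-size statement uses three groups for a two-group randomisation, and its reserve of about double compares a total with a per-group figure

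*Protocol article*

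**What the plan says.** All the sizing text is in the Study 4 section of the protocol article.

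- Design: "Individuals who agreed to participate in this study are randomly divided into two groups". After a common training course, "the intervention group receives a booster training once every 3 months, whereas the control group does not". No third group is described.
- Sizing: "In the ANOVA between the three groups, effect size was set at 0.25", with alpha 0.05 and power 0.80, from which "the necessary data number will be approximately 50 persons for each group".
- Number set: "the number of subjects is set at a higher 100 persons, which is about double the necessary number". The excess is presented as protection against dropout and missing data. No dropout rate is given.
- Pool: the same section puts the target group at approximately 80 citizens. Table 1 also gives 80, with a sample population of 57.
- Analysis: repeated ANOVA and a mixed effects model for longitudinal change, with assessments every 6 months up to 30 months, and multiple comparison tests between groups.
- Status: the abstract, the list of strengths and limitations, the background, the Study 4 section and the discussion of weaknesses variously call this part exploratory, small or limited in sample size.

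**The concern.** The number of groups in the calculation is not the number randomised. The reserve is obtained by setting a total of 100 against a requirement of 50 that the preceding sentence states per group.

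A reader who takes the paragraph at face value will believe that the study has 80% power for the stated effect and could lose about half its participants and keep it. Neither follows from the stated inputs. This matters most if the booster shows no difference: the paragraph invites the reading that an adequately powered study found nothing.

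**Working it through.** **Inputs (Study 4 section and Table 1).** Effect size 0.25, alpha 0.05, power 0.80; k = 3 groups in the calculation, k = 2 randomised; 50 per group required; 100 persons set; pool about 80; sample 57.

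**Assumptions.** 0.25 is Cohen's f, allocation is equal, and the F test is non-directional. For two equal groups d = 2f, so f = 0.25 is d = 0.5.

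**Step 1: the reserve, from the article's own figures.**
- Two groups: 2 × 50 = 100. The number set equals the requirement, so the reserve is zero.
- Three groups: 3 × 50 = 150. The number set is 100/150 = 67% of the requirement.
- If 100 per group was meant, two groups need 200, against a pool of about 80. Even 100 in total exceeds that pool.

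This step needs no power calculation and no reading of the effect size.

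**Step 2: reproduce the stated 50 per group.** For a one-way ANOVA, power = P(F′ > F crit), where F′ is noncentral F with df1 = k − 1, df2 = N − k and λ = N·f² = 0.0625·N.
- k = 3, N = 150: λ = 9.375, power 78.0%.
- k = 3, N = 158: λ = 9.875, power 80.2%. This is the smallest N reaching 80%. With equal groups it becomes 159, or 53 per group.

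The stated figure of about 50 is therefore close to a three-group one-way ANOVA with f = 0.25. The gap between 50 and 53 looks like rounding and carries no weight here. The near match supports reading 0.25 as Cohen's f.

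**Step 3: the same inputs for two groups.** k = 2, N = 128: λ = 8.0, power 80.1%. The need is 64 per group before any dropout.

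**Step 4: one-way power at the numbers in the article, no dropout.**

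| N | λ | Two groups | Three groups |
|---|---|---|---|
| 100 | 6.25 | 69.7% | 58.9% |
| 80 | 5.00 | 59.8% | 48.7% |
| 57 | 3.56 | 45.8% | 35.7% |

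Assumed dropout of 10% to 30% from 100 lowers two-group power to between 65% and 54%.

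**Step 5: detectable effect at 57, two groups.** Solving for 80% power gives f = 0.378, so d = 2 × 0.378 = 0.76. That is 0.378/0.25 = 1.5 times the stated effect.

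**Step 6: how far the planned longitudinal model changes this.** Assume six measurements (baseline plus five six-monthly visits to 30 months) and an equal correlation ρ between them. For the between-group test of a repeated ANOVA, λ = N·f²·m/(1 + (m − 1)ρ). At N = 57, two groups:
- ρ = 0.3: λ = 57 × 0.0625 × 6/2.5 = 8.55, power 82%.
- ρ = 0.9: λ = 57 × 0.0625 × 6/5.5 = 3.89, power 49%.

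At N = 100 the same range is 97% to 73%. The article gives no correlation and does not base its 80% on this model.

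**The case against.** **The study is declared exploratory.** It is called exploratory or small in several places, and no confirmatory claim rests on the 80%. This stands and lowers the severity. It does not make the paragraph correct: the paragraph still asserts 80% power and a twofold reserve, and it now sits beside text calling the sample limited.

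**The longitudinal analysis may have more power.** This also stands. A reader might infer from Step 4 that the trial has under 50% power with its 57 participants. The documents do not support that. The 46% is for a single, unadjusted, one-way comparison, and Step 6 gives about 49% to 82% at 57 over the correlations shown. A group-by-time test can give more still: 88% at 57 with two measurements and ρ = 0.3 if 0.25 is taken as the interaction f. But with two groups and two measurements that f means a difference in change of 4 × 0.25 = 1.0 SD, not the 0.5 SD of the one-way case. None of this was offered as the basis of the stated figure.

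**Perhaps three is right.** The Methods section mentions a Study 4a that is not explained, and multiple comparison tests suit more than two groups. A reader might infer that three is simply a slip and 128 the correct target. The article does not settle this, so the group count has to be reconciled before any one total is adopted. No third group is described, and 100 falls short of the one-way requirement either way.

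**A one-sided test reaches about 80% at N = 100.** It does (79.9%, no dropout), but with no reserve, and it falls to 71.6% at 80 and 58.7% at 57. The stated ANOVA is non-directional.

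**57 is a recruitment result.** True: the plan never claims 80% at 57. The figure matters for reading the results, not as an input to the calculation.

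**Conclusion.** The point holds for the sample-size statement as written. Two parts need no assumption about the effect size: the calculation uses three groups where two are randomised, and 100 persons is not double the requirement on any reading that the pool of about 80 allows.

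The power shortfall holds for the stated one-way inputs: 128 needed for two groups or about 159 for three, against 100 set and 57 in the sample. It rests on f = 0.25, equal allocation, a non-directional test at 0.05 and no dropout. It is not a statement of the power of the planned repeated-measures or mixed model, which depends on a correlation the article does not give.

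Severity is moderate. The error affects what a null result can be taken to mean, but the exploratory status already limits the claims that can be made.

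**What to change.** 1. Reconcile the number of groups in the calculation with the randomised design, or describe the third group if there is one.
2. Remove the claim of an approximately twofold reserve. State whether each figure is per group or in total, and reconcile 100 with the pool of about 80.
3. Restate the requirement for the reconciled design. For two groups, one-way, f = 0.25: 128 evaluable in total before dropout. At the 57 in Table 1: power about 46%, or detectable f about 0.38 (d about 0.76).
4. Say that these figures are for a one-way comparison. If power is claimed for the repeated-measures or mixed model, state the number of measurements, the within-person correlation and the effect being tested, and show a range (for example, about 49% to 82% at 57 for correlations 0.9 to 0.3 with six measurements).
5. Report Study 4 as estimates with confidence intervals, in line with its exploratory status, and do not present a null result as adequately powered.

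The cost is wording and a less favourable stated power. No participant, visit or procedure changes.
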